## Abstract

Introduction: Leucorrhoea is natural vaginal discharge caused by hormonal changes, pregnancy, or sexual stimulation. This study protocol describes the methodology for a 12-week yoga program on the symptoms of leucorrhoea disorder among adult females.

Methods and analysis: The present study is a two-armed, randomized parallel-group, active-control trial for patients with blinded outcome assessors and multiple primary and secondary outcomes. The appropriate sample size will be determined based on the findings of the feasibility study. The participants will be recruited from a hospital and research centre in Madhya Pradesh, India. Individuals who meet the inclusion criteria for leucorrhoea disorder will be chosen following laboratory examinations. Randomization will be used to assign the chosen individuals to either the intervention or control groups (1:1). For adult females with leucorrhoea disorders, the intervention will consist of a yoga-based program that will run for one hour, five days a week, for 12 weeks. Data will be collected at baseline and post-intervention, in the 12th week. The outcome measures will include various primary (colour, odour, amount, vaginal culture, vaginal smear, and imbalance of various gonad hormones) and secondary (lower abdominal pain and quality of life) outcomes. The analysis will involve intention-to-treat and per-protocol approaches that will evaluate the impact of yoga on various outcome measures and will be assessed using statistical tests.

Ethics and dissemination: The study has been approved by the Institution Ethics Committee of Lakshmibai National Institute of Physical Education. Written informed consent will be obtained from each participant before inclusion. Results will be available through research articles and conferences. The summary of key results in layman's language will be made publicly available through newspaper articles.

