Randomization will be performed between two groups of participants. The vaginal discharge assessment form should be filled out by all the participants. After obtaining written consent from the participants and confirmation through a lab report by the gynaecologist about the patient's condition, pre-testing will be conducted, and data will be collected on the selected variables. The obtained data will be tabulated as baseline data. Before starting the intervention program, an interactive introductory lecture will be conducted. In the introductory lecture, the purpose and design of the study will be explained to the participants. A structured yoga module for managing leucorrhoea was developed, incorporating yoga postures, breathing techniques, meditation, and relaxation practices. The module was validated by 20 experts, who recommended the most effective practices based on their expertise. This validated protocol aims to provide a holistic, non-invasive approach to managing leucorrhoea symptoms (such as lower abdominal pain, lower back pain, fatigue, weakness, etc.). Yoga practices will be taught to the participants for 12 weeks. After the completion of three months of intervention, the lab reports and psychological assessments will be collected for the second time by the researcher, and the data will be tabulated for the statistical procedure.

Yoga intervention procedure

The yoga intervention will involve weekly group sessions, conducted five days a week for 60 minutes, from 6:00 AM to 7:00 AM. Participants will learn and practice specific yoga poses, breathing exercises, and meditation techniques tailored to address the symptoms and concerns associated with leucorrhoea. The sessions will be led by a certified yoga instructor, with instructional materials and resources provided to support home practice. This intervention aims to promote physical and mental well-being, reduce stress levels, and improve the overall quality of life for individuals with leucorrhoea. The waitlist control group will not receive any intervention during the study period but will be offered the yoga program after the study’s completion, based on their interest. The description of yoga practices is given in Table 1 [17-19].

**Table 1 TAB1:** Description of Yoga Practices.

Yogic Practices	Timing/Rest	Description

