Moola bandha (perineum contraction)	3 rounds × 90 sec; 10 sec rest	It stimulates the pelvic nerves and tones the urogenital and excretory systems. Moola bandha is both a means to attain sexual control (brahmacharya) and to alleviate a multitude of sexual disorders. It enables sexual energy to be directed either upward for spiritual development [18].
Uddiyana bandha (abdominal contraction)	3 rounds × 90 sec; 10 sec rest	It creates a suction pressure that reverses the flow of the sub-pranas, apana and prana, uniting them with Samana. there is an explosion of subtle force that travels upward through Sushumna Nadi [18].
Concentration on Swadhisthana chakra	5 min	Swadhisthana is associated with the organs of excretion and reproduction. Visualisation of this centre can help rectify disorders of these functions [18].
Closing prayer: "Asato mā sad gamaya, tamaso mā jyotir gamaya, mṛtyor māmṛtaṁ gamaya" [17].		Prayer should be chanted followed by explaining the meaning. Translation: "Lead us from ignorance to knowledge, from darkness to light and from death to immortality."

Measures to maintain adherence

Yoga classes will be provided free of charge and conducted within a radius of 1 km from the hospital. The yoga practices will be implemented throughout the study duration, with participants receiving regular reminders and support from the researcher to encourage adherence to the prescribed regimen. Weekly check-ins will be conducted to address any concerns, resolve difficulties, and offer guidance as needed. Attendance will be recorded for all sessions to monitor compliance. The intervention consists of 12 weeks of yoga sessions, conducted five days a week, totalling 60 sessions. A minimum attendance of 48 sessions (80% adherence) will be required to include participants’ data in the analysis. These measures aim to ensure a high level of adherence and maximize the intervention’s effectiveness in managing leucorrhoea.

Outcome measures

The research personnel will conduct screening for potential participants. Further participants will be asked to report any adverse events, i.e., injury resulting from the program, and will be advised to consult their physician to provide care as appropriate.

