The evaluation will primarily involve descriptive analysis to summarize the baseline characteristics and outcomes. To assess the effectiveness of the intervention, a global statistical test (GST) will be applied. The pre-treatment characteristics of the sample will be compared with those of the target population, and a per-protocol analysis will be conducted.

For continuous variables (e.g., age, hormone levels, and duration of symptoms), the mean and standard deviation (SD) or median and interquartile range (IQR) will be used to summarize the baseline data. A comprehensive examination of the treatment’s objectives will also be performed. Missing data will be addressed using various imputation techniques, and sensitivity analyses will be conducted to assess the robustness of the results. To estimate log-binomial models, generalized estimating equations (GEE) will be applied, while mixed-effects linear regression models will be used to analyze the data.

Outcomes will be evaluated both at baseline and after 12 weeks, with all available data considered in the analysis. Statistical analyses will be performed using IBM SPSS, Version 21, and JASP. A significance level of p<0.05 will be applied throughout the analysis.

Ethical statement

The study protocol is approved by the Institutional Ethics Committee of Lakshmibai National Institute of Physical Education, Gwalior issued approval IEC/LNIPE/01/2022/05. The trial has been registered in the Clinical Trial Registry of India - CTRI/2022/11/047474, and the study was conducted in accordance with the principles of the Declaration of Helsinki. 

The consent of participants in the research study will be obtained, and their privacy and confidentiality will be maintained throughout the study. Any potential risks or discomforts associated with the study will be minimized, and participants will be provided with adequate information to make an informed decision about their participation. The results of the study will contribute to a better understanding of the effectiveness of yoga in managing leucorrhoea disorders and may have implications for future treatment options.

Confidentiality

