## Results

After completing data collection and analysis, the results will be systematically compiled and presented in a clear and concise manner. Descriptive analysis will be used to summarize the baseline characteristics of the participants, with continuous variables (e.g., age, hormone levels, and duration of symptoms) being summarized using the mean and standard deviation (SD) for normally distributed data or median and interquartile range (IQR) for non-normally distributed data. Categorical variables will be presented using frequency counts and percentages. The effectiveness of the intervention will be assessed using a global statistical test (GST) to compare the pre-treatment features of the sample with those of the target population. A per-protocol analysis will be conducted to evaluate the intervention’s impact on outcomes, including changes in symptoms and quality of life.

Missing data will be addressed using appropriate imputation techniques, and sensitivity analyses will be conducted to ensure the robustness of the results. To estimate log-binomial models, generalized estimating equations (GEE) will be used. Additionally, mixed-effects linear regression models will be applied to assess the impact of the intervention, with outcomes measured at both the baseline and after 12 weeks. Results will be shared with participants and stakeholders, and the findings will be disseminated through academic publications and conference presentations to maximize the study’s impact and contribution to the field.

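### As written, the 48-of-60-session attendance rule decides whose data are analysed; in practice it can exclude only yoga participants after randomisation, and it conflicts with the stated intention-to-treat approach

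*Protocol article*

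**What the plan says.** The attendance rule is in the section on measures to maintain adherence. The programme is described first: "The intervention consists of 12 weeks of yoga sessions, conducted five days a week, totalling 60 sessions". The condition follows: "A minimum attendance of 48 sessions (80% adherence) will be required to include" a participant's data in the analysis. Nothing in that section limits the condition to one of several analysis sets.

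Four other places bear on it:

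- **Yoga intervention procedure**, on the comparator: "The waitlist control group will not receive any intervention during the study period".
- **Abstract**, on analysis sets: "The analysis will involve intention-to-treat and per-protocol approaches".
- **Data Analysis** names one analysis set, "and a per-protocol analysis will be conducted", and then says "Outcomes will be evaluated both at baseline and after 12 weeks, with all available data considered in the analysis". It also plans imputation of missing data with sensitivity analyses.
- **Results** again names one set: "A per-protocol analysis will be conducted to evaluate" the effect of the intervention on outcomes.

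Intention-to-treat appears only in the Abstract.

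**The concern.** Attendance is observed after randomisation, and only one arm has sessions to attend. A rule that admits data according to attendance therefore compares a selected part of the yoga arm with an unselected waitlist arm, and randomisation no longer protects that comparison. Women who manage at least 48 sessions at six in the morning over 12 weeks may differ from the rest in health, motivation or early improvement. If they do, a difference between arms can appear even when yoga has no effect.

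Participants cannot be blinded, and pain and quality of life are self-reported, so a selection effect would add to any reporting effect already present. The rule also reduces the number analysed in the yoga arm.

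This is not a detail left to a fuller document. The article states a rule, and that rule disagrees with its own description of the analysis.

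**Working it through.** **1. The plan's own figure.** 12 weeks × 5 days = 60 sessions, and 48/60 = 0.80. Both reproduce.

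**2. Whom the rule can remove.** Waitlist participants have 0 sessions during the study. Taken literally, 0 < 48 removes every control and leaves no comparison. Any workable reading applies the rule to the yoga arm only.

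**3. The statements side by side.**

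| Section | Whose data are analysed |
|---|---|
| Abstract | Intention-to-treat and per-protocol |
| Measures to maintain adherence | Only those with at least 48 sessions |
| Data Analysis | Per-protocol is the only set named; all available data; imputation |
| Results | Per-protocol is the only set named |

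A set cut down to attenders is not an intention-to-treat set. Discarding collected data for low attendance is not using all available data. The second row cannot stand beside the first, or beside the all-available-data statement in the third, unless it is limited to the per-protocol set.

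**4. Size of the possible bias.** From the article: 40 per arm (Randomization and blinding) and two-sided 0.05 (Sample Size Estimation). Assumed, because the article gives neither:

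- *q*, the share of the yoga arm below 48 sessions;
- ρ, the correlation between attendance and a better outcome.

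Further assumptions are no true effect and one continuous, normally distributed outcome compared at 12 weeks without baseline adjustment.

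With attendance and outcome bivariate normal, bias in SD units = ρ·φ(z_q)/(1−q), where z_q is the normal quantile at *q*.

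Example, *q* = 0.20 and ρ = 0.5:

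- φ(z_q) = 0.280, so bias = 0.5 × 0.280/0.80 = 0.175 SD.
- About 40 × 0.80 = 32 yoga participants remain against 40 controls, so SE = √(1/32 + 1/40) = 0.237 SD.
- The test statistic shifts by 0.175/0.237 = 0.74. The two-sided error is P(Z > 1.96 − 0.74) + P(Z < −1.96 − 0.74), about 0.11.

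A simulation of 20,000 trials per setting (two-sample t test) agrees with the formula. In the table, bias is from the formula and type I error from the simulation.

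| Excluded from yoga arm | ρ | Bias (SD) | Two-sided type I error |
|---|---|---|---|
| 10% | 0.2 | 0.039 | 0.052 |
| 10% | 0.5 | 0.097 | 0.070 |
| 20% | 0.2 | 0.070 | 0.059 |
| 20% | 0.3 | 0.105 | 0.073 |
| 20% | 0.5 | 0.175 | 0.113 |
| 30% | 0.2 | 0.099 | 0.067 |
| 30% | 0.3 | 0.149 | 0.087 |
| 30% | 0.5 | 0.248 | 0.170 |
| 20% | 0 | 0 | 0.050 |
| 20% | −0.3 | −0.105 | 0.071 |

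Positive bias favours yoga. At ρ = −0.3 it runs against yoga. With all 40 analysed in each arm (*q* = 0) there is no selection bias, and the error is 0.05.

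**The case against.** **The sentence may only have been meant to define the per-protocol set.** The article announces a per-protocol analysis and defines it nowhere else. An 80% attendance threshold is a natural definition, and the literal reading, which removes every control, can hardly be intended. On that reading the sections agree. This is plausible, so the documents do not support the inference that the trial will in fact analyse attenders only. But the sentence refers to the analysis without qualification, and the two sections that describe the analysis name no other set. The text has to settle it.

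**A reader might infer that intention-to-treat cannot be carried out.** That goes too far. Data Collection and Outcome Measures plan the post-intervention assessments without an attendance condition, so only the wording of the rule stands in the way. One remark under Sample Size Estimation, which ties data collection to the experimental group performing the practices for 12 weeks, is less reassuring. It is a reason to say explicitly that low attenders are assessed.

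**A reader might infer a definite bias towards yoga.** The documents do not show one. Nothing in them says how attendance relates to outcome. Women whose symptoms resolve could stop coming, and the bias would then reverse.

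**The illustration is not the planned analysis.** The article plans mixed models using baseline and 12-week data, log-binomial models and a global test, and several primary outcomes are not continuous. Using baseline would remove bias that comes from stable differences between attenders and others; bias from a link between attendance and change would remain. The 20% attrition allowance under Sample Size Estimation is not an adherence rate and does not fix *q*. These limits stand: the figures show a plausible order of size, not the trial's error rate.

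**Which set is primary may be left to a fuller document.** That is fair as far as omission goes. It does not answer the stated rule.

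**Conclusion.** The point holds as a rule that is wrong as written and at odds with the rest of the article. If the 48-session condition governs the main analysis, it is a one-arm, post-randomisation exclusion and can bias the comparison. The likely direction is towards yoga if regular attenders would have done better anyway, but this is a judgement and not a finding from the text.

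Under the stated assumptions and ρ from 0.2 to 0.5, the bias is 0.07 to 0.17 SD with type I error of about 6% to 11% when 20% of the yoga arm is excluded. When 30% is excluded, it is 0.10 to 0.25 SD with about 7% to 17%. At 10% excluded the effect is small. There is no bias at ρ = 0, and it changes sign for ρ < 0.

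The conflict between the sections does not depend on any of these assumptions. It should be resolved before analysis, and preferably while 12-week assessments can still be obtained from women who attended fewer sessions.

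**What to change.** - **Measures to maintain adherence:** replace the inclusion condition with a statement that attendance at 48 or more of the 60 sessions defines the yoga participants in a secondary per-protocol set. Say how waitlist participants enter that set, since they have no sessions.
- **Data Analysis and Results:** state that the primary analysis includes every randomised participant in the assigned arm whatever the attendance, that the planned 12-week assessment is sought from all of them, and that the per-protocol analysis is secondary. This brings both sections into line with the Abstract.
- **Optional:** if the effect among adherers is of interest, a complier-average (instrumental-variable) estimate can be added. The correction does not depend on it.

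The cost is wording, plus the effort of obtaining 12-week assessments that are already planned from women who attended little. The estimated effect may be smaller than in the adherent subset.

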## Results

After completing data collection and analysis, the results will be systematically compiled and presented in a clear and concise manner. Descriptive analysis will be used to summarize the baseline characteristics of the participants, with continuous variables (e.g., age, hormone levels, and duration of symptoms) being summarized using the mean and standard deviation (SD) for normally distributed data or median and interquartile range (IQR) for non-normally distributed data. Categorical variables will be presented using frequency counts and percentages. The effectiveness of the intervention will be assessed using a global statistical test (GST) to compare the pre-treatment features of the sample with those of the target population. A per-protocol analysis will be conducted to evaluate the intervention’s impact on outcomes, including changes in symptoms and quality of life.

Missing data will be addressed using appropriate imputation techniques, and sensitivity analyses will be conducted to ensure the robustness of the results. To estimate log-binomial models, generalized estimating equations (GEE) will be used. Additionally, mixed-effects linear regression models will be applied to assess the impact of the intervention, with outcomes measured at both the baseline and after 12 weeks. Results will be shared with participants and stakeholders, and the findings will be disseminated through academic publications and conference presentations to maximize the study’s impact and contribution to the field.

## Discussion

The present study aims to investigate the effectiveness of a yoga-based lifestyle modification program on managing leucorrhoea. By incorporating both biochemical and qualitative assessments, the trial will provide a comprehensive evaluation of yoga’s impact on key indicators such as hormonal balance, inflammation, and the frequency and severity of symptoms. Participants will be carefully selected based on confirmed diagnoses of leucorrhoea, ensuring homogeneity of the sample. The experimental group will practice a structured yoga program, including asanas and breathing exercises, while the control group will maintain their usual lifestyle, serving as a comparative baseline.

**Figure 2 FIG2:**
[figure not shown]
Hypothetical mechanism of action for the effectiveness of yoga in managing leucorrhoea: stress reduction, circulatory enhancement, hormonal balance, and pelvic floor strengthening

The hypothetical mechanism of action for yoga’s effectiveness includes stress reduction, improved circulation, hormonal balance, and pelvic floor muscle strengthening, all of which are interconnected. These mechanisms are hypothesized to improve vaginal health, reduce abnormal discharge, and alleviate associated symptoms. This integrative approach, illustrated in the flowchart, aligns with the holistic nature of yoga and emphasizes its potential as a non-invasive treatment option.

The COVID-19 pandemic has heightened health awareness, encouraging women to seek proactive approaches to well-being [30]. During recruitment, participants meeting the inclusion criteria will be informed about the holistic benefits of yoga and encouraged to participate consistently throughout the study. This emphasis on informed consent and patient engagement is expected to enhance adherence and outcomes. By combining robust methodology with evidence-based yoga practices, this trial has the potential to contribute significantly to the field of complementary therapies for women’s health. The study design ensures validity and reliability, making it a valuable framework for future research. The results are anticipated to advance understanding of yoga’s role in managing leucorrhoea and promote its practical applications in reproductive health care.

## Conclusions

This protocol establishes a framework to assess the efficacy of yoga practices in managing leucorrhoea, aiming to improve symptoms and well-being while contributing valuable insights into women’s health and complementary therapeutic approaches.
